**Methods:**

This prospective, 2-arm, multicenter observational study will assess and compare the clinical effectiveness and economic value of collaborative treatment versus UC alone for patients with primary headache disorders. Adults aged ≥19 years with a primary diagnosis of primary headache disorders visiting participating hospitals under South Korea’s national collaborative treatment pilot project will be enrolled. Participants will receive either collaborative treatment (integrating WM pharmacotherapy with KM therapies such as acupuncture, pharmacopuncture, and herbal medicine) or UC (monodisciplinary care with WM or KM alone) based on informed choice. Clinical and cost-related outcomes will be assessed at baseline and 6 and 12 weeks. Clinical outcomes include monthly headache days, the numeric rating scale, the Headache Impact Test, the EQ-5D-5L, and the EuroQol visual analogue scale. The cost-effectiveness evaluation includes the cost per quality-adjusted life year, the incremental cost-effectiveness ratio, and the cost-effectiveness acceptability curve. Both intention-to-treat and per-protocol analyses will be performed.

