**Assessments**									
	MHDs^a^			✓		✓		✓	
	NRS^b^			✓		✓		✓	
	HIT-6^c^			✓		✓		✓	
	EQ-5D-5L			✓		✓		✓	
	EQ-VAS^d^			✓		✓		✓	
	Cost information					✓		✓	
	Hospital medical records and administrative data							✓	

^a^MHD: monthly headache day.

^b^NRS: numeric rating scale.

^c^HIT-6: Headache Impact Test.

^d^EQ-VAS: EuroQol visual analogue scale.

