A nonrandomized observational design was adopted to reflect real-world clinical settings where patient preference acts as a crucial determinant of treatment adherence and outcomes. Consequently, participants will exercise informed choice regarding their treatment modality. During the consultation, practitioners will provide comprehensive information on the expected benefits, potential side effects, and cost implications of both collaborative treatment and UC. On the basis of this shared decision-making process, patients will select their preferred treatment group, ensuring that the study findings mirror actual health care use patterns in South Korea. If a participant opts for collaborative treatment, one practitioner will initiate a collaborative treatment request to the other practitioner. Treatment choices can be adjusted at any time through consultation with practitioners, and all treatments will be recorded and monitored. Patients who agree to participate will be given detailed information about the study and all safety-related aspects before they provide informed consent. After obtaining written consent, a medical doctor or a KM doctor will assess the participant’s eligibility. Those who meet the inclusion criteria will be enrolled in the study and assigned an enrollment number to preserve anonymity. To ensure fair and open participation, announcements about the study will be made publicly available at the participating institutions.

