#### Cost-Effectiveness

Cost use for both treatments will be comprehensively assessed, including direct medical costs, direct nonmedical costs, and indirect costs such as productivity losses, derived from CRFs and hospital administrative data. The cost-effectiveness of the treatments will be evaluated using several measures: cost per quality-adjusted life year (QALY) [48,49], the incremental cost-effectiveness ratio (ICER) [50], and the cost-effectiveness acceptability curve (CEAC) [51]. The cost per QALY will be estimated using the area under the curve method [48,52] based on utility scores captured through the EQ-5D-5L and EQ-VAS. The ICER, representing the economic value of collaborative treatment compared with UC, is determined by dividing the incremental cost by the incremental QALYs gained [50,53]. The CEAC illustrates the probability that a treatment is cost-effective across a range of willingness-to-pay thresholds per QALY, with the horizontal axis denoting willingness-to-pay values and the vertical axis representing the corresponding probabilities [51,54].

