Utility values from the EQ-5D-5L and EQ-VAS will be used to estimate QALYs using the area under the curve method [48]. Deterministic analyses for the ICER will be performed using both ITT and per-protocol data from a limited societal perspective and a societal perspective. A probabilistic sensitivity analysis will also be carried out using parameter distributions and estimates. To account for sampling uncertainty in the ICER point estimates, 95% CIs will be calculated using the bootstrapping method or a seemingly unrelated regression model. All statistical analyses will be conducted using Stata/MP (version 14.0; StataCorp) and SAS (version 9.4; SAS Institute), with the significance level set at a *P* value of <.05.

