### Strengths and Limitations

The strength of this study lies in its real-world, multicenter design within South Korea’s national health care framework, enhancing the generalizability of the findings. To our knowledge, this is the first study to comprehensively evaluate both the clinical effectiveness and cost-effectiveness of collaborative treatment for primary headache disorders. In interpreting the findings, certain methodological considerations inherent to this observational design should be noted. While the nonrandomized design and patient-driven treatment choices introduce potential selection bias, these features are inherent to observational studies reflecting actual clinical practice. To rigorously mitigate these factors, we will use generalized linear mixed models to control for baseline differences and injury mechanisms. Additionally, although the exclusion of patients covered by automobile insurance may limit generalizability to specific posttraumatic cases, this criterion aligns with the current operational guidelines of the national collaborative treatment pilot project. Regarding potential heterogeneity across institutions, standardized treatment protocols based on CPGs have been implemented across all centers to ensure consistency. Finally, cost data derived from patient self-reports will be cross-verified where possible to minimize recall bias. Finally, as this study is embedded within South Korea’s dual health care system, the findings may have specific relevance to similar integrative models but require careful adaptation for countries with different health care structures.

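### The economic analysis of self-selected groups names no adjustment of incremental costs or QALYs for baseline utility or confounders, though the data to do so are already collected

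*Protocol article*

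**What the plan says.** Allocation is by patient preference. Under Participants and Treatments: "On the basis of this shared decision-making process, patients will select their preferred treatment group". The same paragraph says that practitioners discuss cost implications before the choice is made. Strengths and Limitations concedes that "the nonrandomized design and patient-driven treatment choices introduce potential selection bias". The Introduction makes cost-efficiency part of the primary objective, next to clinical effectiveness.

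The second paragraph of Statistical Analyses describes a generalized linear mixed model for between-group effects at each time point. It adjusts for age, sex, onset duration, diagnosis and comorbidities. The list is introduced as examples and does not name baseline utility, income or insurance status. Income and insurance status are collected under Baseline Characteristics.

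The economic analysis has its own description:

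- QALYs (Statistical Analyses): "Utility values from the EQ-5D-5L and EQ-VAS will be used to estimate QALYs using the area under the curve method".
- ICER (Cost-Effectiveness): it "is determined by dividing the incremental cost by the incremental QALYs gained".
- Data sets (Statistical Analyses): "Deterministic analyses for the ICER will be performed using both ITT and per-protocol data".
- Sampling uncertainty (Statistical Analyses): "95% CIs will be calculated using the bootstrapping method or a seemingly unrelated regression model".

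A probabilistic sensitivity analysis and a CEAC are also planned. No covariate is named for any of these.

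On the timing of cost data, the abstract says "Clinical and cost-related outcomes will be assessed at baseline and 6 and 12 weeks". In Table 1 the row "Cost information" is marked at 6 and 12 weeks only.

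**The concern.** In a preference-based comparison the groups may differ at baseline in severity, quality of life, income and insurance. Because cost is part of the counselling that precedes the choice, selection may bear on the cost side as well as on health.

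QALYs have a specific weakness here. The area under the utility curve includes the baseline value, which treatment cannot have changed. If the groups start at different utilities, that difference counts as QALYs gained or lost unless baseline utility is adjusted for. Bootstrapping and probabilistic sensitivity analysis describe sampling and parameter uncertainty; neither removes confounding.

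At stake is the economic half of the primary objective. The protocol says its results should help optimise reimbursement models. Over 12 weeks the QALY denominator is small, so a modest baseline difference can move the ICER and the CEAC a long way.

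**Working it through.** The protocol states no expected cost, QALY or ICER, so there is no planned figure to reproduce. The check takes the visit schedule from the protocol and assumes the utility values.

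**Inputs from the protocol.** Utilities at weeks 0, 6 and 12; QALYs by area under the curve.

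**Assumed, not in the protocol.** Baseline utility gap 0.02 to 0.05; true utility gain 0.02 to 0.05 at both follow-up visits; share *r* of the baseline gap that persists at follow-up.

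**Step 1, weights.** By the trapezoid rule in years,

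QALY = (3·u0 + 6·u6 + 3·u12)/52.

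The weights are 3/52 = 0.0577, 6/52 = 0.1154 and 3/52 = 0.0577, which sum to 12/52 = 0.2308. Baseline utility carries 3/12, one quarter of the total.

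**Step 2, QALY difference due to a baseline gap.** This is gap × (3 + 9r)/52.

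| Gap | Baseline term only (r = 0) | Half persists (r = 0.5) |
|---|---|---|
| 0.02 | 0.02 × 3/52 = 0.0012 | 0.02 × 7.5/52 = 0.0029 |
| 0.05 | 0.05 × 3/52 = 0.0029 | 0.05 × 7.5/52 = 0.0072 |

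**Step 3, QALY difference due to a true gain.** This is gain × 9/52.

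- Gain 0.02: 0.0035 QALY.
- Gain 0.05: 0.0087 QALY.

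**Step 4, bias relative to the true gain.** This is (gap/gain) × (3 + 9r)/9. If gap and gain are equal, it is 33% (r = 0) to 83% (r = 0.5). With a gap of 0.02 and a gain of 0.05, it is 0.4 × 33% = 13% to 0.4 × 83% = 33%.

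**Step 5, effect on the ICER, cost difference held fixed.** Take a true gain of 0.03, worth 0.03 × 9/52 = 0.0052 QALY, and let r run from 0 to 1.

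- A gap of 0.02 to 0.03 favouring collaborative treatment gives 0.0063 to 0.0121 QALY, so the ICER is 0.82 to 0.43 times its adjusted value.
- The same gap in the other direction gives 0.0040 down to −0.0017 QALY, so the ICER is 1.3 to 9 times its adjusted value, or changes sign.

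**Step 6, can the QALY difference cross zero by chance alone?** Assume 140 per group (312 × 0.9/2 ≈ 140, equal groups), utility SD 0.10 to 0.15 and between-visit correlation 0.5.

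- SD of the QALY = SD × √(54 + 45)/52 = SD × 0.191, where 54 = 3² + 6² + 3² and 45 = 2 × 0.5 × (18 + 9 + 18).
- SE of the difference = SD × 0.191 × √(2/140) = 0.0023 to 0.0034.
- For gains of 0.02 to 0.03 (0.0035 to 0.0052 QALY), gain/SE is about 1.0 to 2.3, so about 16% to 1% of bootstrap differences would be negative.

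Once that share exceeds 2.5%, the 95% interval for the QALY difference includes zero and a confidence interval for the ratio is hard to interpret.

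**The case against.** The strongest reply is that the text is silent, not wrong. A reader might infer that the plan divides raw group differences. The documents do not say so: neither raw nor unadjusted appears, and a ratio of increments describes an adjusted ICER just as well. This is a journal article, and an economic regression's covariate list can sit in a fuller document.

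Some text also points towards adjustment. The paragraph with the adjusted model opens by covering both clinical effectiveness and cost-effectiveness. The EQ-5D-5L and EQ-VAS are among the clinical outcomes, so utilities at each visit may fall under that model. Strengths and Limitations names mixed models as the control for baseline differences without limiting this to clinical outcomes. Seemingly unrelated regression can carry covariates. It is therefore too strong to say that the economic result has no protection against selection.

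These points limit the claim but do not remove it. A per-visit model does not by itself adjust a 12-week QALY or a total cost, and nothing carries its adjustment into the ICER. The regression is given one purpose, a confidence interval, and is interchangeable with a bootstrap that adjusts for nothing. The article does describe confounder control and does describe the economic estimators, but does not connect them.

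Three further inferences go too far:

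- That the bias rivals any plausible 12-week gain. The 33% to 83% figure arises when the assumed gap equals the assumed gain; other inputs give less or more.
- That QALY differences will probably cross zero. On the assumptions in step 6 this is plausible but not certain, and the planned CEAC remains interpretable if they do.
- That differences in prior resource use are beyond adjustment because Table 1 has no baseline cost entry. Treatment history, medication use, income and insurance status are collected and can serve as partial proxies.

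**Conclusion.** The point holds as a nearly free improvement. For a self-selected comparison the protocol specifies adjustment of the clinical model but none for incremental costs or QALYs. It does not establish that the analysis will be unadjusted.

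If the economic part is carried out with only what is written, baseline utility enters each QALY at one quarter of the weight and any imbalance passes into the ICER and CEAC. For assumed gaps of 0.02 to 0.05 this is 0.0012 to 0.0029 QALY from the baseline term alone and 0.0029 to 0.0072 if half persists, against 0.0035 to 0.0087 for assumed true gains of 0.02 to 0.05. That can be material, in either direction.

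The quarter weight follows from the visit schedule and is firm. The sizes rest on assumed gaps, gains and persistence. The disagreement between the abstract and Table 1 on baseline cost data is a separate, minor inconsistency.

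**What to change.** In the economic paragraph of Statistical Analyses, state that:

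1. Incremental costs and incremental QALYs are estimated jointly by seemingly unrelated regression, bootstrapped within group.
2. The QALY equation includes baseline EQ-5D-5L utility.
3. Both equations include baseline severity, the confounders of the clinical model, institution, and the income and insurance status already collected.
4. The ICER and CEAC are built from these adjusted increments.
5. Incremental net monetary benefit with its 95% CI is reported alongside the ICER, because a confidence interval for the ratio can be uninterpretable if QALY differences cross zero.

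Separately, reconcile the abstract with Table 1 on whether cost information is taken at baseline. A new recall item on prior costs is not recommended as an adjuster: recruitment began in August 2025, so the item would be missing for everyone already enrolled.

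The cost is a paragraph of wording, modest programming and one correction to the abstract or Table 1. No new data are needed. The adjustment removes only confounding by measured variables, and the limitations section should continue to say that selection bias may remain.

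### The planned 95% CI for the ICER is unbounded if the QALY difference is not clearly different from zero; incremental net benefit with a CI should carry the inference

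*Protocol article*

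**What the plan says.** The Cost-Effectiveness section defines the ICER as a ratio that "is determined by dividing the incremental cost by the incremental QALYs gained". On the denominator, Statistical Analyses says: "Utility values from the EQ-5D-5L and EQ-VAS will be used to estimate QALYs using the area under the curve method". The abstract fixes the time points: "Clinical and cost-related outcomes will be assessed at baseline and 6 and 12 weeks".

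On sampling uncertainty in the ICER point estimates, Statistical Analyses states that "95% CIs will be calculated using the bootstrapping method or a seemingly unrelated regression model". The ICER is to be calculated in both the ITT and the per-protocol data and from two perspectives, so several such intervals are planned.

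Two other tools are planned. The Cost-Effectiveness section has an acceptability curve: "The CEAC illustrates the probability that a treatment is cost-effective across a range of willingness-to-pay thresholds per QALY". Statistical Analyses adds: "A probabilistic sensitivity analysis will also be carried out using parameter distributions and estimates". Net benefit is not named anywhere.

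**The concern.** A confidence interval for a ratio behaves well only when the denominator is clearly away from zero. If it is not, two things go wrong.

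- The interval with correct coverage (Fieller) has no finite pair of limits. It is either the whole line or everything outside a finite gap.
- Bootstrap ratios stop being ordered. A replicate with lower cost and more QALYs (dominant) and one with higher cost and fewer QALYs (dominated) can give the same negative number. If the ratios are sorted and cut at the 2.5th and 97.5th percentiles, two finite limits still appear, so the failure is silent.

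Cost-effectiveness is part of the primary objective and of the hypothesis in the Introduction. A published ICER interval will therefore be read, even when it has no usable meaning.

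**Working it through.** **Plan's own figure.** There is none for this point: the article gives no utility difference, utility SD, QALY difference or ICER. Only the sample size is used here. From Sample Size Estimation, 312 × 0.9 = 281, or about 140 evaluable per group. The 1:1 split is an assumption, because patients choose their treatment.

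**Condition for a bounded interval.** Write dQ for the QALY difference and dC for the cost difference. The Fieller limits R solve (dC − R·dQ)² = 1.96²·Var(dC − R·dQ). The coefficient of R² is dQ² − 1.96²·SE(dQ)². The interval is bounded only if this is positive, that is, if |dQ|/SE(dQ) > 1.96.

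**QALY difference.** With visits at 0, 6 and 12 weeks the trapezoid weights are (3, 6, 3)/52. With no baseline difference and the same utility gain g at 6 and 12 weeks, dQ = g × 9/52. For g = 0.02, dQ = 0.0035.

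**SE without baseline adjustment** (assumed: correlation 0.6 between all visits, utility SD s of 0.10 to 0.15).
- Variance factor: 9 + 36 + 9 + 2 × 0.6 × (18 + 9 + 18) = 108.
- SD of QALYs: s × √108/52 = 0.020 to 0.030.
- SE: SD × √(2/140) = 0.0024 to 0.0036.

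**SE with adjustment for baseline utility** (same assumptions).
- Residual variance at each follow-up visit 1 − 0.36 = 0.64; residual covariance 0.6 − 0.36 = 0.24.
- Variance factor: 36 × 0.64 + 9 × 0.64 + 2 × 18 × 0.24 = 37.44.
- SD of QALYs: s × √37.44/52 = 0.0118 to 0.0177. SE = 0.0014 to 0.0021.

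**Results.** The share of replicates at or below zero is Φ(−dQ/SE). The smallest observed gain that gives a bounded interval is 1.96 × SE × 52/9.

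| | Unadjusted | Baseline-adjusted |
|---|---|---|
| Replicates ≤ 0, observed gain 0.01 | 23-32% | 11-21% |
| Replicates ≤ 0, observed gain 0.02 | 7-17% | 0.7-5% |
| Observed gain needed for a bounded interval | 0.027-0.041 | 0.016-0.024 |

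**Wider range.** This takes correlation 0.5, utility SD 0.10 to 0.20, 140 per group, and both adjusted and unadjusted analyses. The probability that the interval is not finite, P(|Z| < 1.96), by true utility difference, is:

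| True difference | Interval not finite |
|---|---|
| 0 | 95% |
| 0.01 | 79-93% |
| 0.02 | 37-88% |
| 0.03 | 7-79% |
| 0.05 | 0-53% |
| 0.08 | 0-14% |

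A simulation of Fieller intervals (3000 runs per scenario, SD 0.15, baseline-adjusted) agrees: 95%, 87%, 66%, 37% and 3% non-finite at differences of 0, 0.01, 0.02, 0.03 and 0.05.

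**A check that needs no utility SD.** The NRS figures behind the sample size (1.85, SD 1.66; 2.48, SD 2.13) give a standardised difference of 0.63/1.910 = 0.33. With 140 per group, z = 0.33 × √70 = 2.76. If the QALY effect were equally large in SD units (an assumption), the interval would be non-finite with probability about Φ(1.96 − 2.76) = 21%. At half that size, z = 1.38 and the probability is about 72%.

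**Net benefit.** INB = λ·dQ − dC is linear in both differences, so its SE is always finite. For illustration, take the adjusted SE of 0.00225 (SD 0.15, correlation 0.5), assumed cost SDs of KRW 0.7m and 0.5m, and no correlation between costs and QALYs. The 95% half-width is then about KRW 0.17m at λ = 20m and 0.26m at λ = 50m.

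**The case against.** The strongest reply is that the plan already contains a sound summary. At each threshold the acceptability curve is in effect the probability that incremental net benefit is positive. It handles all four quadrants and remains valid when the QALY difference is near zero. The probabilistic sensitivity analysis is likewise unaffected. That stands, and it limits the point. But the curve gives no estimate with a CI, and it sits beside the ICER interval without correcting it.

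Second, the article names neither percentiles nor any rule for negative ratios, and seemingly unrelated regression supplies the joint covariance that a Fieller interval or net benefit needs. How the interval is built may be settled in a plan that is not shown. This also stands: sorting replicate ratios is one possible reading of the bootstrap, not the stated method. The commitment to an interval for the ratio is stated, however, and a Fieller interval is unbounded under the same condition.

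Third, the unadjusted figures are the unfavourable case. Baseline EQ-5D-5L is collected and regression permits adjustment, though the article does not say that the QALY analysis will use it. Both cases are therefore shown.

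A reader might infer that the QALY difference will be close to zero because follow-up lasts only 12 weeks. The documents do not support this. They fix the horizon, which caps QALYs at 12/52 = 0.231 per patient, but give no effect size. Nor is the horizon the cause: with a constant utility effect, the difference and its SE shrink together and their ratio does not change.

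**Conclusion.** The point holds as a minor one. The plan commits to a 95% CI for a ratio whose denominator may not be clearly different from zero, and in that case the interval is unbounded or cannot be read. How likely this is depends on utility effects and SDs that the article does not give. Under the assumptions shown, a bounded interval needs an observed utility gain of about 0.03-0.04 unadjusted or 0.016-0.024 adjusted. Failure is likely at true differences of 0.01, ranges from 37% to 88% at 0.02, and is uncommon (0-14%) at 0.08. All of this assumes about 140 evaluable patients per group in a 1:1 split.

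A reader might also infer that the whole economic conclusion rests on this interval. The documents do not make the ICER interval a decision rule, and the acceptability curve and probabilistic sensitivity analysis remain usable. Design and data collection are not affected.

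**What to change.** In Statistical Analyses, replace the sentence on ICER confidence intervals with the following plan:

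- Report incremental net monetary benefit with its 95% CI at pre-stated willingness-to-pay values, from the same bootstrap or seemingly unrelated regression output. This is the inferential result.
- Show it beside the acceptability curve and the cost-effectiveness plane.
- Give the ICER as a point estimate, with a CI (for example Fieller) only when the QALY difference is clearly non-zero. A simple rule is that its own 95% CI excludes zero.

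The cost is a change of analysis wording, with no extra patients, visits or data. The downside is that willingness-to-pay values must be fixed in advance. Data collection is expected to run to December 2027, so this can still be done before results are known.
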